### Interventions

According to consort and trend guidelines for intervention reporting
[72], the rationale for the intervention selection as well as the specification of how the qualities and delivery of the therapeutic modalities are expected to impact targeted outcomes are presented below. The therapeutic modalities used share many therapeutic goals and similarities in the way they combine information from different sensory modalities aiming at enhancing various brain functions. However, due to the way the methods are organized they differ somewhat in terms of dosage.

#### Rhythm and music-based therapy program

We use a method of multi-sensory stimulation of the brain which is based on rhythm and music and originally developed by jazz drummer Ronnie Gardiner. The therapy program, designed to help people with injuries and diseases of the central nervous system
[73] is called Ronnie Gardiner Rhythm and Music method (RGRM™) and has since 1993 been implemented in health care and rehabilitation in Sweden. The method is based on the principle of neuroplasticity
[34], and uses rhythm, music, colour, the voice, text, shapes and movement to stimulate coordination, balance, endurance, attention, memory, body image and social interactions. RGRM™ uses a unique note system (illustrated in Figure
2) that combines red and blue body symbols with corresponding sound codes and body movements. The symbols represent hands and feet and are displayed on a screen. The colours represent right and left brain activity, with the right brain (red) governing the left side of the body, and left brain (blue) governing the right side of the body. In total, there are 18 specific body movements and participants carry out the movements by clapping hands, tapping their hands on their knees and stamping their feet on the floor, without using any other tools than their own bodies.

**Figure 2 F2:**
[figure not shown]
The RGRM note system with corresponding sound codes.

The note system may be combined in a number of ways in order to stimulate different parts of the brain. A certified RGRM™ practitioner creates a piece of movement coordination (chorescore) and participants coordinate the series of movements while saying its name, all accompanied with rhythm and music. Through the stimulation of senses and the rhythmic activation of body movements and accompanying sound codes (derived from drum sounds), the right- and left-hand sides of the body are activated simultaneously, together with the stimulation of the left- and right brain hemispheres. The level of difficulty is adjusted with regard to the level of mobility and capabilities of the participants. At their individual pace the participants perform increasingly more complex sequences of rhythmic composite movements. If a participant cannot perform a certain movement the person is instructed to initiate/imagine the movement. The following parameters were selected as the intervention in the group T1 and T3: two sessions per week for twelve weeks, each session of 90 min in duration broken into 10 segments including a coffee break and concluded by a summary.

#### Therapeutic riding

TR is s multi-sensory treatment modality that combines physical activity with cognitive stimulation and emotional connection with the horse. Its goal is to improve posture, balance, coordination, muscular strength and cognitive functions, while offering an opportunity to improve motivation and self-esteem. The rhythmic and repetitive walking motion of a horse resembles the human walking gait, and the many textures, sounds and sights provide an enriched environment. We selected the following parameters as the intervention in the group T2: two sessions per week for twelve weeks, each session of 240 minutes in duration consisting of two segments, interaction with the horse prior to or after riding, and the riding itself. The treatment also includes preparation of the horse (grooming and equipping the horse with shabrack, voltage girth and bridle before the riding session, or their removal afterwards). The sessions are concluded by eating lunch or having refreshments together with the therapists and assisting personnel.

The TR is performed at a riding centre adapted for disabled and the riding sessions are held mostly outside in the paddock and inside during bad weather conditions. The sessions take place in groups of two to six participants who ride in pairs for 30 minutes, while the others are bystanders. The treatment plan as well as appropriate horses, equipment and exercises are selected in order to facilitate treatment goals, and to provide the most effective treatment for each patient along the intervention period. The sessions are led by a physiotherapist and an occupational therapist who both have strong equine background, as well as knowledge of disabilities related to stroke and education in TR.

Two assistants prepare the horses and lead them during the riding sessions and assist during the mounting on a ramp and the dismounting on the ground. During riding the participant sits on a shabrack (thick soft cover) and as a safety precaution, one assistant walks alongside the horse and another assistant leads the horse. Each riding session begins and ends with *relaxation and body awareness exercises* – deep, slow breathing, focusing and relaxing body parts starting out from shoulders towards feet, partly with the eyes shut while instructed to feel the horse’s movements through their own body. The mounted exercises are individually tailored to the subjects’ physical needs and ability to ride and include the following: 1. *Balance exercises*: maintaining balance while holding one or both arms sideways; putting the hand/hands on the head; riding in diagonals, circles, over low poles and weaving through cones; 2. *Trunk rotation*: reaching for the horse’s tail; holding a stick with both hands with elbows at the waist and then rotating the trunk to the sides; 3. *Exercises designed to train participants’ affected body parts*: simulating bicycling with the legs; reaching for the horse’s ears; lying prone with the arms around the horse’s neck and then rising again; grasping a tennis ball from the instructor in different directions; controlling the horse by holding the reins; 4. *A cognitive component*: taking part in the planning of the participant’s own riding in different directions and exercises; paying attention to the other equipage in the paddock while riding; following multiple oral instructions. Whenever the horse moves or when changes in speed or direction take place, postural adjustment is required. All exercises are, if possible, performed while the horse is moving and mostly the subjects ride at a walking pace although some participants try a few laps of trot.

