## Methods

### Study design

A single blinded three-armed randomized controlled trial is designed with the aim to evaluate whether it is possible to improve overall health status and functioning of individuals in the late phase of stroke (1-5 years after stroke) through a rhythm and music-based therapy program or TR (Trial registration: Clinical Trials.gov Identifier: NCT01372059). The term *single blinded* refers to the evaluators in the trial being unaware of the nature of the treatment the participants are receiving. About 120 individuals will be consecutively and randomly allocated to one of three groups: (T1) rhythm and music-based therapy program; (T2) TR; or (T3) control group that receives the T1 therapy a year later. Evaluation is conducted prior to and after the 12-week long intervention, and three and six months after completed intervention. The evaluation comprises comprehensive functional and cognitive assessment (both qualitative and quantitative), and questionnaires. Blood samples will be collected pre-, post intervention and at the three and six month follow-up with the aim of identifying potential biomarkers predictive of outcome. Based on the International classification of functioning, disability, and health (ICF), the outcome measures are classified into six comprehensive domains, with participation as the primary outcome measure assessed by the Stroke impact scale (SIS, version 2.0.). The secondary outcome measures are grouped within the following domains: body functions, activity, environmental factors and personal factors. Life satisfaction and health related quality of life constitute an additional domain. The trial design is illustrated in Figure
1. Ethical approval was granted by the Regional Ethical Review Board in Gothenburg (Ref number: 698-09) and the study is conducted in accordance with relevant ethical guidelines.

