### Sample size

The calculation of sample size is based on a clinically relevant difference to be detected across the two main arms of the trial with an alpha level of 5% and a power goal of 80%. A Chi-square test was used for statistical calculations in Nquery 6.0. The required sample size was determined on the basis of one of the items included in the primary stroke-specific, comprehensive, health status outcome measure - Stroke Impact Scale (SIS). SIS measures the aspects of stroke recovery which were found to be important to patients and caregivers as well as stroke experts. The questions of the SIS are broken down into eight domains: strength, hand function, mobility, activities of daily living, emotion, memory, communication, and social participation. The first four of these domains may be combined into one physical domain, but in order to more clearly track changes based on the patient’s particular set of symptoms, the other four items are scored separately. One additional item is included in the SIS to assess the subject’s overall perception of recovery. This item 9 – “Stroke recovery” is presented in the form of a visual analogue scale from 0 to 100 where 0 indicates “no recovery” and 100 indicates “full recovery”.

Based on a previous study indicating that the item of stroke recovery in SIS is a good measure of individual patient’s changes due to rehabilitation
[69], and the heterogenic characteristic of the study population, the required sample size was determined based on this specific item. The minimal important difference (MID) was determined a priori. On the basis of previous estimates
[70], MID was set at 10 points of the total range of the scale in item 9. Thus, a change of 10 points is considered to represent a meaningful difference. An absolute difference between the two groups of 30% is defined to be a clinically meaningful difference with regard to the item stroke recovery in SIS. Based on this estimate, at least 41 patients would be required in each of the three groups for the results to satisfy the power criteria of 80%.

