### Statistical analysis

Outcome variables will be analyzed according to an intention-to-treat model including all randomized patients for whom a baseline value exists in the primary outcome variable. Those who withdraw will be assigned an outcome score identical to their baseline score i.e. no change. In addition, the per-protocol analysis will be restricted to the participants who complete the treatment program and remain in the group to which they were randomly assigned, and have available data on the primary and secondary outcome variables. Patients will be excluded from the per-protocol analysis if they withdrew during the intervention phase or undergo a co-intervention during the three-month intervention phase. Reasons for early withdrawal will be noted.

Baseline and demographic characteristics will be summarized using descriptive statistics. Statistical difference between treatments with respect to the item “stroke recovery” is to be tested using the chi-square test (Mantel Haenzel corrected for gender and hemispheric location) by dichotomizing data into categories *improved* or *unchanged/deteriorated* with respect to change from baseline to follow-up, where improvement/clinically meaningful change is defined as any increase equivalent to 10 points of the total range of the scale. Un-ordered categorical data will be analyzed using the Mantel Haenzel chi-square approach. Analysis of covariance (ANCOVA) will be used to determine whether there are any differences between the control and intervention groups in post-intervention evaluation scores for continuous data, with baseline scores used as covariates in the analysis, and gender, hemispheric location and intervention as fixed factors. Qualitative data from the interviews and focus groups will be analyzed using content analysis as described by Malterud
[71]. Unsupervised algorithms will be used to analyze the plasma profiles in search for predictive biomarkers and biomarker patterns predictive of therapeutic success. For the primary and secondary analyses, missing data will be replaced using a conservative method, i.e. last observation carried forward (LOCF). All tests will be two-sided and with p<0.05 as a level of significance.

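### Riding is given in groups of two to six, but the stated tests treat riders as independent, so the riding-versus-control standard error may be understated

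*Protocol article*

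**What the plan says.** **Delivery.** In the Therapeutic riding section: "The sessions take place in groups of two to six participants who ride in pairs for 30 minutes". There are two sessions a week for twelve weeks, so 24 sessions of 240 minutes, each closing with food or refreshments taken together. For the rhythm and music programme the article gives session frequency, length and content, but no group size, and it does not say outright that sessions are shared.

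**Control.** T3 receives the T1 programme a year later. The last evaluation is six months after a 12-week intervention, so T3 is untreated throughout the comparison.

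**Analysis.** The stroke recovery item is dichotomised and tested by Mantel-Haenszel chi-square, corrected for gender and hemisphere. Continuous outcomes go into an ANCOVA with baseline as covariate and "gender, hemispheric location and intervention as fixed factors". On the significance level: "All tests will be two-sided and with p<0.05 as a level of significance".

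**Sample size.** "A Chi-square test was used for statistical calculations in Nquery 6.0". The target is stated thus: "An absolute difference between the two groups of 30% is defined to be a clinically meaningful difference". The result is that "at least 41 patients would be required in each of the three groups". The Study design section says: "About 120 individuals will be consecutively and randomly allocated to one of three groups", which is about 40 per arm.

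**The concern.** Riders in one group spend 24 long sessions together. They ride in pairs, watch each other and eat together. Peers and group climate are part of what is delivered, and the recovery item is self-rated, so some positive correlation within riding groups is plausible. T3 participants have no such grouping. If the correlation is there, the T2 mean carries a between-group variance component that neither stated test allows for. The confidence interval for T2 versus T3 would then be too narrow, and the test would reject a true null more often than 5% of the time.

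This is a comment on what the article states, not on something left out. It names the tests and lists the factors in the model, and that model assumes independent participants.

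**Working it through.** **Step 1. Does the plan's own figure allow for grouping?** Inputs from the Sample size section are a two-sided alpha of 5%, power of 80% and a difference of 30 percentage points. The base rate is not stated. The usual chi-square formula without continuity correction, where p̄ is the mean of the two proportions, is

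n = [1.96·√(2p̄(1−p̄)) + 0.8416·√(p₁(1−p₁)+p₂(1−p₂))]² / 0.30²

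At 25% versus 55%, p̄ = 0.40 and n = (1.358 + 0.555)² / 0.09 = 40.7, so 41. The same formula gives 41 at 45% versus 75%, and 39 to 43 for base rates from 20% to 50%. The stated 41 is thus reproduced as a calculation for independent individuals, with no allowance for grouping.

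**Step 2. Effect of grouping on T2 versus T3.** Group size m runs from 2 to 6 (Therapeutic riding section). The ICC is an assumption, with range 0.01 to 0.10. Arms are taken as equal in size and total variance.

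- Design effect in T2: DE = 1 + (m−1)·ICC. In T3 it is 1.
- Variance inflation of the difference: v = (DE + 1)/2.
- Ratio of true to assumed standard error: √v.
- Actual type I error of the stated test: 2·[1 − Φ(1.96/√v)].

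| m | ICC | DE | v | SE ratio | Actual error |
|---|---|---|---|---|---|
| 2 | 0.01 | 1.01 | 1.005 | 1.002 | 5.1% |
| 2 | 0.10 | 1.10 | 1.050 | 1.025 | 5.6% |
| 4 | 0.02 | 1.06 | 1.030 | 1.015 | 5.35% |
| 4 | 0.05 | 1.15 | 1.075 | 1.037 | 5.9% |
| 6 | 0.05 | 1.25 | 1.125 | 1.061 | 6.5% |
| 6 | 0.10 | 1.50 | 1.250 | 1.118 | 8.0% |

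At ICC = 0, v = 1 and nothing changes. With mixed group sizes the effective m lies between 2 and 6, so the range still holds.

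**Step 3. Power in the worst assumed case (m = 6, ICC 0.10), starting from exactly 80%.** The standardised effect is 1.96 + 0.84 = 2.80.

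- Stated test, unadjusted: Φ(0.84/√1.25) = Φ(0.75), about 77%, but at an actual error of 8.0%.
- Test adjusted for grouping: Φ(2.80/√1.25 − 1.96) = Φ(0.55), about 71%, at the intended 5%.

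**Step 4. Number of riding groups.** About 40 riders give 40/6 ≈ 7 to 40/2 = 20 groups.

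**The case against.** The case against has several strands.

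- **The correlation is assumed.** The article gives no ICC, and with groups this small the effect may be negligible. This stands. The 8.0% needs the largest group and the highest assumed ICC together; the middle case is 5.9%.
- **T1 is not described as group-delivered.** A reader might infer shared sessions from the screen, the coffee break and the plural participants, then apply a riding-sized group to T1 and conclude that T1 versus T2 is affected most. Group delivery is plausible, but neither it nor a group size is stated. No figure for T1 versus T3 or T1 versus T2 can be supported.
- **Therapists and season.** A reader might count these as further sources of clustering. The article describes one physiotherapist and one occupational therapist at one riding centre. If they led every group, therapist would not vary between riding groups. T3 participants are also allocated and assessed over calendar time, so season is not peculiar to the active arms. Only peers and group climate carry the argument.
- **Stable membership is not stated.** If riders moved between groups, a single identifier would describe the exposure poorly. This stands as a condition on the fix.
- **This is a condensed article, and a fuller analysis plan may exist.** That plan might contain a sensitivity analysis for grouping, and the article contradicts none of its own numbers here. But the article does fix the tests and factors, and the comment concerns those as stated.

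**Conclusion.** The point holds conditionally and for T2 versus T3. That comparison is partially nested by the article's own description, and the stated tests neither accommodate nor estimate a within-group correlation. If the correlation is positive, the standard error is understated by a factor of 1.00 to 1.12, and the actual type I error is about 5.1% to 8.0%. These figures rest on group sizes of two to six from the article, an assumed ICC of 0.01 to 0.10, equal arms and reasonably stable groups.

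Two stronger readings are not supported. One is that the standard errors are definitely too small: that needs an ICC which the article does not give. The other is that grouping cuts the power of the planned test to 71%: that figure belongs to the adjusted test in the worst assumed case, where the planned test keeps about 77%. For T1 the concern is open until its delivery format is known. The size is negligible to moderate; the change is worth making because it is cheap and recruitment and follow-up were still in progress.

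**What to change.** 1. Record each participant's therapy group. This assumes that membership can be recovered for the 84 participants who have already completed the intervention, and that it was mainly stable. Because the identifier reveals allocation, keep it with the allocation list until the last follow-up is complete.
2. State whether T1 is delivered in groups and, if so, their size.
3. Fit the ANCOVA with its present covariate and factors plus a therapy-group random effect in the group-delivered arm or arms only. Treat each T3 participant as a singleton and use small-sample degrees of freedom.
4. Give the responder result with a clustered variance corrected for few groups, since an uncorrected robust variance is unreliable with 7 to 20 clusters.
5. Report the ICC with its interval.

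If the stated tests are to remain primary, specify items 3 to 5 as a sensitivity analysis before the data are analysed.

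The cost is one variable and a somewhat more complex model. Intervals will be wider if the ICC is positive, and power for T2 versus T3 falls to about 71% in the worst assumed case. The planned 40 or so per arm leaves no margin over the required 41 to absorb this. The ICC estimate from so few riding groups will be imprecise.

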### Evaluation procedure

At baseline, group equality will be determined regarding all descriptive and baseline variables.

The effects of the interventions are evaluated using a pre- and post-test design. The baseline evaluation phase precedes randomization and takes place 1−3 weeks prior to the first intervention session. The post-intervention evaluation is undertaken within 1−3 weeks and approximately six month after intervention completion, comprising the whole measurement battery. At three months after completion of the intervention phase, all study questionnaires are completed and blood samples are collected. A research coordinator, a nurse, a physiotherapist and a neuropsychologist perform the evaluation of participants throughout the trial. At all evaluation phases, measurements are being carried out in the same sequence throughout the trial. All questionnaires are posted to the participants beforehand, in order to have them completed prior to the appointment with the research coordinator. In order to ensure that the completion of the questionnaire has been correctly performed, the research coordinator goes through the questionnaire together with the participants by face-to-face interviews. The individual interviews are performed within four weeks after end of treatment and the focus groups are conducted six months after completion of the intervention by two experienced persons (occupational therapist and speech therapist), the latter being responsible for interviewing aphasic participants.

#### Measures of participant entry characteristics

The participant characteristics recorded are: gender, age, time since stroke onset both at entry to the trial and at each evaluative period (days), the type and site of the stroke lesion, previous stroke insult(s) in the same hemisphere, level of educational attainment and handedness. The Modified Rankin Scale (MRS) is used to describe the degree of disability or dependence in daily activities among the participants
[74]. To describe the level of dependence/independence in personal and instrumental activities of daily living among the participants, the *ADL Staircase* is used
[75],
[76]. *The National Institutes Health Stroke Scales (NHISS)* are used to describe neurological deficit among the participants
[75,77].

#### Outcome measures

Reliable and valid measures are used for the outcome assessment and are classified according to the different domains of the ICF
[66,78,79]. The ICF definitions are presented in Table
1. The outcome measures describe overall health status and functioning at six different perspectives: 1. *Body functions*: including the following subcategories: perceived physical and mental functioning and cognitive function; 2. *Activities;* 3. *Participation*; 4. *Environmental factors;* 5. *Personal factors* and 6. *Life satisfaction and quality of life* (not part of the ICF). The outcome measures used within each domain are presented in Figure
3, and the outcome measure abbreviations are listed in Table
2. For the below listed outcome measures sum scores are calculated when appropriate.

**Table 1 T1:** ICF definitions

**Terminology**	**Definition**
Body functions/structure	Physiological functions of body systems including psychological. Structures are anatomical parts or regions of their bodies and their components. Impairments are problems in body function or structure.
Activity	The execution of a task by an individual. Limitations in activity are defined as difficulties an individual might experience in completing a given activity.
Participation	Involvement of an individual in a life situation. Restrictions to participation describe difficulties experienced by the individual in a life situation or role.

